## Supplementary Methods

### Statistical analyses

#### Outcome measures

The plan for analysis of the data was decided upon before the commencement of the analyses and was formulated by the Researchers based on scientific rather than statistical grounds. Furthermore, and given the longitudinal nature of the data it was decided to fit a mixed model in each case, with a random intercept for each participant. Time in all cases was fitted as a categorical fixed effect.

Time and group were fitted as fixed effects along with their interaction. Participant ID was fitted as random effect with the inclusion of age, disease stage, disease duration and LEDD (Levodopa dosage).

The model was fitted for all outcome variables. Following the analyses, the resultant models objects were processed in order to derive appropriate estimated marginal means. All mixed model analyses was performed in R using “lmerTest”, “tidyverse”, “flextable”, “openxlsx”, “janitor”, and “emmeans”, and custom written codes in R.

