| Exploratory Outcomes                                                                                                                                                                                                                                                                                                                                                          |                            |                            |                         |               |            |                          |              |                      |
| PDQ-39 total score                                                                                                                                                                                                                                                                                                                                                            |                            |                            |                         |               |            |                          |              |                      |
| BL                                                                                                                                                                                                                                                                                                                                                                            | 37.61 (30.93 to 44.28); 27 | 30.29 (23.96 to 36.62); 30 | -7.31 (-16.40 to 1.78)  | 0.12          | WK4-BL     | -5.38 (-7.95 to -2.81)   | <0.0001      | 0.05                 |
| Wk4                                                                                                                                                                                                                                                                                                                                                                           | 29.46 22.79 to 36.13); 27  | 27.69 (21.25 to 34.13); 26 | -1.77 (-10.93 to 7.39)  | 0.71          | WK6-BL     | -6.81 (-9.38 to -4.24)   | <0.0001      |                      |

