| Wk6                                                                                                                                                                                                                                                                                                                                                                           | 27.87 (21.19 to 34.54); 27 | 26.42 (19.98 to 32.86); 26 | -1.44 (-10.60 to 7.72)  | 0.76          | WK6-WK4    | -1.43 (-4.01 to 1.15)    | 0.53         |                      |
| BDI-II total score                                                                                                                                                                                                                                                                                                                                                            |                            |                            |                         |               |            |                          |              |                      |
| BL                                                                                                                                                                                                                                                                                                                                                                            | 11.60 (8.97 to 14.23); 27  | 10.20 (7.71 to 12.70); 30  | -1.40 (-4.99 to 2.19)   | 0.45          | WK4-BL     | -1.50 (-2.81 to -0.19)   | 0.07         | 0.23                 |
| Wk4                                                                                                                                                                                                                                                                                                                                                                           | 9.08 (6.45 to 11.71); 27   | 9.72 (7.16 to 12.29); 26   | 0.64 (-2.99 to 4.28)    | 0.73          | WK6-BL     | - 1.84 (-3.15 to -0.53)  | 0.02         |                      |

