### 6.2. Data analysis and statistical methods

Descriptive statistics will be calculated for demographic characteristics for the full study cohort and by light therapy study group. Categorical variables will be summarised as percentages and continuous variables will be summarised by medians, means with standard deviations. Participants will be analysed according to the light therapy group as randomised. Analysis will follow an intention to treat principle with missing values accounted for in the statistical model. Mixed models will be used to account for the longitudinal nature of the data, using intervention group, time point (baseline, week 4 and week 6) and interactions as explanatory variables to the primary, secondary and exploratory outcome measures in R applying packages. The fitted mixed models will be used in *post hoc* analyses with respect to group and time point to explore potential differences due to these two variables and their interaction. The mixed models will be adjusted for baseline characteristics including age, sex, Hoehn and Yahr disease stage, PD duration and levodopa equivalent daily dosage (LEDD).

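### The random-intercept-only model imposes one variance and one correlation on all three visits; if that fails, standard errors of the change-from-baseline group contrasts can be wrong in either direction

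*Combined protocol and SAP*

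**What the plan says.** Supplementary Methods (Statistical analyses, Outcome measures) sets out the model: "it was decided to fit a mixed model in each case, with a random intercept for each participant". It adds "Time in all cases was fitted as a categorical fixed effect" and "Time and group were fitted as fixed effects along with their interaction", with age, disease stage, disease duration and LEDD included. The scope is complete: "The model was fitted for all outcome variables", so the primary polysomnography and DLMO outcomes are covered.

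The section names no random slope, residual correlation structure, visit-specific variance, robust standard error or covariance sensitivity analysis. Protocol section 6.2 is less specific: "Mixed models will be used to account for the longitudinal nature of the data", with no covariance structure named.

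The Endpoints page makes change from baseline to week 4 and to week 6 primary. The schedule and section 5.5 (item 5) give light from baseline to week 4, then two weeks without it.

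**The concern.** A random intercept with a single residual variance treats any two visits of a participant as equally alike. In this design there are reasons to doubt that. Baseline and week 4 lie four weeks apart on either side of the start of light. Week 4 and week 6 are two weeks apart, and the light is withdrawn between them. Participants may also respond differently, which would change the variance or correlation after baseline.

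At stake is the precision of the contrasts that match the primary endpoints, namely the difference between groups in change from baseline to week 4 and to week 6. Both borrow one pooled error term. If one visit pair is more or less alike than the average pair, its standard error is too large or too small. Degrees-of-freedom corrections do not repair a wrong covariance. With complete data the point estimates are unaffected; with missing visits they can shift too.

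**Working it through.** **1. What the reported results show.** Section 6.1's total of 60 plays no part here. The relevant reported figures are the 95% intervals for the time contrasts in Table S1. For PDQ-39 these include "5.38 (-7.95 to -2.81" for week 4 minus baseline and "1.43 (-4.01 to 1.15" for week 6 minus week 4 (both estimates are negative in the table). Half-width = (upper − lower)/2, for example (7.95 − 2.81)/2 = 2.57.

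| Outcome | wk4−BL | wk6−BL | wk6−wk4 |
|---|---|---|---|
| PDQ-39 | 2.57 | 2.57 | 2.58 |
| BDI-II | 1.31 | 1.31 | 1.31 |
| MDS-UPDRS total | 3.59 | 3.55 | 3.63 |
| MDS-UPDRS motor | 2.29 | 2.27 | 2.33 |

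The largest ratio within an outcome is 2.33/2.27 = 1.03. This is what a random-intercept fit to nearly balanced data produces whether or not its assumption is true.

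**2. The constraint.** Under the model, Var(y_j) = σ_b² + σ_e² and Cov(y_j, y_k) = σ_b², so Var(y_j − y_k) = 2σ_e² for every pair. With balanced data, the fitted 2σ_e² estimates the mean of the three true pairwise difference variances.

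**3. Consequence.** With equal visit variances σ², the true variance for a pair is 2σ²(1 − ρ_jk). Hence

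model SE / true SE = √[(1 − mean ρ)/(1 − ρ_jk)],

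type I error ≈ 2[1 − Φ(1.96 × ratio)].

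Example at 0.5/0.5/0.8: mean ρ = 0.6; for either baseline contrast the ratio is √(0.4/0.5) = 0.894, giving 8.0%.

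**4. Range.** The correlations below are assumptions, because the documents give none. Order: BL–wk4/BL–wk6/wk4–wk6. Simulation: 27 versus 30 participants (the baseline numbers in Table S1), complete data, equal variances, 40,000 trials per row, nominal 5%.

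| Correlations | SE ratio wk4−BL, wk6−BL | Formula | Simulated wk4−BL, wk6−BL | Simulated 2-df group x time |
|---|---|---|---|---|
| 0.6/0.6/0.6 | 1.00, 1.00 | 5.0%, 5.0% | 4.8%, 5.2% | 4.9% |
| 0.6/0.6/0.7 | 0.957, 0.957 | 6.1%, 6.1% | 6.1%, 5.9% | 5.1% |
| 0.5/0.5/0.7 | 0.931, 0.931 | 6.8%, 6.8% | 7.0%, 6.8% | 5.4% |
| 0.5/0.5/0.8 | 0.894, 0.894 | 8.0%, 8.0% | 7.9%, 8.0% | 6.0% |
| 0.4/0.4/0.8 | 0.882, 0.882 | 8.4%, 8.4% | 8.2%, 8.5% | 6.3% |
| 0.7/0.7/0.5 | 1.106, 1.106 | 3.0%, 3.0% | 3.1%, 3.0% | 5.4% |
| 0.5/0.7/0.5 | 0.931, 1.202 | 6.8%, 1.9% | 6.8%, 1.9% | 5.3% |

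With a contrast-specific error, which is what an unstructured covariance gives for complete data, the two baseline contrasts stay between 4.8% and 5.2% in every row.

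**5. Group difference at a single visit.** With equal variances this stays between 4.8% and 5.2% in every row, because it rests on total variance rather than on the pair correlations. With assumed SDs of 1/1.3/1.3 and a common correlation of 0.6, it becomes about 2%, 7% and 7% at baseline, week 4 and week 6.

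**The case against.** A random intercept with three visits is a common and defensible choice, and several limits on the point stand.

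First, a reader might infer from the near-identical half-widths in Table S1 that the model misfits. They do not show that: they identify the model that was fitted. They also cover exploratory outcomes only, and are time contrasts pooled over both arms.

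Second, the between-group results tabulated there are by-visit differences and one group-by-time p-value, not pairwise group-by-time contrasts. By-visit differences are unaffected under equal variances, and the 2-df test moves by about one percentage point at most in these scenarios. However, the endpoints are worded as change from baseline to each visit, and the pairwise contrast is the quantity that matches them.

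Third, the direction is unknown. A closer week 4–week 6 pair makes both baseline contrasts anti-conservative. Withdrawal of light could instead bring week 6 back towards baseline, and then the week-6 contrast is conservative (the 0.5/0.7/0.5 row).

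Fourth, the half-widths imply an average correlation of roughly 0.75 to 0.85 for the exploratory outcomes, higher than most values assumed here. This does not remove the effect, because only the relative sizes of 1 − ρ matter. At 0.8/0.8/0.9, mean ρ = 0.833, the ratio is √(0.167/0.2) = 0.913 and the type I error is about 7.4%.

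Finally, week 6 versus week 4 is not a listed endpoint, so loss of precision there carries little weight.

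**Conclusion.** The point holds as a cheap improvement. The specified model imposes equal variances and one correlation on all visit pairs, and the plan has no check on either. If the assumption fails, the week-4 and week-6 group-by-time contrasts for change from baseline can have a true type I error of about 3% to 8% instead of 5% (1.9% to 8.5% across the simulated rows). If it holds, there is no harm. The figures rest on assumed correlations, equal variances and complete data.

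The stronger reading, that the primary standard errors are wrong or too small, is not supported: the documents contain no visit variances or correlations for any outcome, so neither the presence nor the direction of an error can be established from them.

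**What to change.** Keep the fixed effects as they are. Fit a repeated-measures model with an unstructured 3 x 3 within-participant covariance, by REML with Kenward-Roger degrees of freedom, and take the week-4 and week-6 group-by-time contrasts from it. Prespecify the random-intercept model, preferably with cluster-robust standard errors, as the fallback for non-convergence or sparse outcomes. Likely candidates are MDS-UPDRS (Enhanced Mel falls from 30 at baseline to 17 and 18 in Table S1) and the bed-partner PSQI score, which exists only where there is a bed partner.

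The cost is a sentence or two in the SAP and a fitting call in a package that supports this covariance, in place of the lmerTest call. There are six covariance parameters instead of two, feasible with about 55 participants. If the common-correlation assumption is true, intervals widen slightly: with 57 participants and complete data, the critical t is 2.00 (55 df) instead of 1.98 (110 df). Outcomes with much missing data may give unstable fits, hence the fallback.

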### Other Secondary (motor)

- Change from baseline to week 4 and week 6 in mean: stride velocity, total double support, balance (average velocity of centre of pressure) and dominant frequency both hands for resting and postural tremor

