#### Other: Environmental light exposure and melanopsin function

The environmental light exposure measured with actigraphy (Geneactive) was analysed using RM-ANOVA (2 lights x 6 time points) in IBM SPSS Statistics (version 29).

Baseline melanopsin function (6sPIPR) in both PD light intervention groups was compared to an age-matched healthy control group (n=10) using One way-ANOVA with Bonferroni corrections in IBM SPSS Statistics (version 29).

Detailed description of all the tests conducted to derive primary, key secondary and secondary outcome measures

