**Figure S2. Melanopsin function (6s PIPR) at baseline, week 4 and week 6**

**A.** The mean post-illumination pupil light response (PIPR %) (95% CIs) as a measure of melanopsin function in both groups randomised to either Daylight Melanopsin (Day Mel:  $n = 27$ , blue columns with blue error bars) or Enhanced Melanopsin (Enhanced Mel:  $n = 28$ , purple columns with purple error bars) compared to an age-matched, healthy control group ( $n = 10$ , black columns with black error bars) at baseline (healthy control data from the Medical Retinal laboratory, QUT). Error bars represent 95% CIs. The higher the PIPR %, the better the melanopsin function. Melanopsin function is significantly reduced in both light intervention groups compared to a healthy age-matched control group ( $p < 0.01$ ). **B.** The PIPR (with 95% CIs) in both groups) at week 4 (Day Mel:  $n = 25$ , Enhanced Mel:  $n = 25$ ) and **C.** at week 6 (Day Mel:  $n = 27$ , Enhanced Mel:  $n = 25$ ), with an increase in melanopsin function in the Enhanced Mel group.

| Time point                                                                                                                                                                                                                                                                                                                                                                    | Day Mel                    | Enhanced Mel               | Mean Difference-Group   | p value Group | Time point | Mean Difference-Time     | p value Time | p value Group x Time |
|-------------------------------------------------------------------------------------------------------------------------------------------------------------------------------------------------------------------------------------------------------------------------------------------------------------------------------------------------------------------------------|----------------------------|----------------------------|-------------------------|---------------|------------|--------------------------|--------------|----------------------|

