## 2. Study objectives

### 2.1. Research questions/ aims

The primary aim is to determine the effect of melanopsin-directed light therapy (daylight melanopsin and enhanced melanopsin) on circadian/sleep behaviour and motor (i.e. gait, balance, tremor) function in optimally medicated people with PD.

The secondary aim is to objectively quantify melanopsin function and its link to circadian and sleep behaviour in PD to define the underlying physiological mechanisms mediating the effect of light in PD.

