### 2.2. Outcome measures

- Primary outcome measures:
  - Change in salivary Dim light Melatonin Onset (DLMO) before and after light intervention at week 4 and week 6.
  - Change in polysomnography parameters (i.e. total sleep time, sleep efficiency and latency and REM latency and time in sleep stages) before and after light intervention at week 4 and week 6.
- Secondary outcome measures:
  - Change in subjective sleep questionnaire results such as in Pittsburgh Sleep Questionnaire Inventory PSQI, Epworth Sleepiness Scale (ESS), Parkinson's Disease Sleepiness Scale before and after light intervention at week 4 and week 6.
  - Other secondary outcome measures are motor function (gait, balance and tremor) and melanopsin-mediated pupil function before and after light intervention at week 4 and week 6.
- Exploratory analysis will examine the effect of light on mood (Beck's Depression Inventory-II and quality of life (PDQ-39) before and after light intervention at week 4 and week 6.

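### Pupil (melanopsin) function at weeks 4 and 6 is a protocol secondary outcome, but the supplement describes no between-arm analysis of it while its figure legend states a rise in one arm; separately, sex is missing from the fitted covariates

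*Combined protocol and SAP*

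**What the plan says.** **Pupil function in the protocol.** Section 2.1 states: "The secondary aim is to objectively quantify melanopsin function and its link to circadian and sleep behaviour in PD". Section 2.2 places among the other secondary outcomes "melanopsin-mediated pupil function before and after light intervention at week 4 and week 6". Section 6.2 applies a mixed model with group, time point and their interaction to the primary, secondary and exploratory outcomes. Table 1 schedules pupillography at all three laboratory visits.

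**Pupil function in the supplement.** The Endpoints section heads its other secondary tier as motor and lists "stride velocity, total double support, balance (average velocity of centre of pressure) and dominant frequency both hands for resting and postural tremor". Pupil function is in none of the four tiers. The Supplementary Methods describe the pupil test together with the screening and chronotype instruments and, unlike the listed endpoints, give it no outcome-measure line. The analysis text, under the heading Other, reads: "Baseline melanopsin function (6sPIPR) in both PD light intervention groups was compared to an age-matched healthy control group (n=10", by one-way ANOVA with Bonferroni correction. Table S1 has no PIPR row. The Figure S2 legend describes means with 95% CIs at baseline, week 4 and week 6, "with an increase in melanopsin function in the Enhanced Mel group".

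**Covariates.** Protocol 6.2 says that the models will be "adjusted for baseline characteristics including age, sex, Hoehn and Yahr disease stage, PD duration and levodopa equivalent daily dosage (LEDD". The supplement, under Outcome measures, says: "Participant ID was fitted as random effect with the inclusion of age, disease stage, disease duration and LEDD (Levodopa dosage".

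**The concern.** Pupil function is the trial's mechanism measure. The secondary aim is to link melanopsin function to sleep and circadian behaviour, and the arms differ in how strongly the light activates melanopsin. A rise in one arm between visits can come from practice, regression to the mean, measurement drift or a change in who was measured. Only the comparison with the other arm separates these from the light. The protocol planned that comparison. The supplement describes none, yet its legend makes a directional statement. A reader cannot tell whether the planned secondary analysis was done, what it showed, or why the outcome lost its tier.

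The covariate mismatch is a smaller matter of traceability. The supplement says that its model was applied to every outcome variable, so the departure from 6.2 would also reach the primary outcomes, and it is neither disclosed nor explained.

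**Working it through.** The documents give no figure to reproduce here. The check is a comparison of texts, with some arithmetic for scale.

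**1. Pupil function, planned against described**

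| Element | Protocol | Supplement |
|---|---|---|
| Status | Other secondary (2.2) | In no tier (Endpoints) |
| Visits analysed | Baseline, week 4, week 6 (2.2, 6.2) | Baseline only (Other) |
| Comparison | Between arms over time (6.2) | Two PD arms against 10 healthy controls |
| Method | Mixed model, group by time (6.2) | One-way ANOVA, Bonferroni |
| Result shown | n/a | Means with 95% CIs by visit; one p value (p < 0.01), for the baseline comparison with controls |

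**2. Who is in the plotted means.** The Figure S2 legend gives Day Mel 27, 25, 27 and Enhanced Mel 28, 25, 25 at baseline, week 4 and week 6. Table S1 shows 27 and 30 at baseline. Take 27 and 30 as the arm sizes (an assumption). The number of Enhanced Mel participants with both a baseline and a week 4 PIPR is then at least 28 + 25 − 30 = 23 and at most 25. The same bounds hold for week 6. So 3 to 5 of the 28 with a baseline value are absent from each later mean, and up to 2 people without a baseline value may be present. The overlap is large but incomplete.

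**3. Precision of the missing contrast.** For a two-arm comparison, in units of the SD of the quantity compared, let s = sqrt(1/n1 + 1/n2). The detectable difference at two-sided 5% is (1.96 + z_power) × s, and the 95% CI half-width is 1.96 × s.

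| Visit | n1, n2 | s | 80% power | 90% power | Half-width |
|---|---|---|---|---|---|
| Week 4 | 25, 25 | 0.283 | 0.79 SD | 0.92 SD | 0.55 SD |
| Week 6 | 27, 25 | 0.278 | 0.78 SD | 0.90 SD | 0.54 SD |

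The comparison is feasible but imprecise. Covariates and repeated measures may tighten it somewhat.

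**4. Sex: how unbalanced could the arms be?** The documents do not give the sex split. If half are men, the SE of the difference in proportions is sqrt(0.25 × (1/27 + 1/30)) = 0.133. A chance gap above 15 points then has probability of about 26%, and above 20 points about 13%.

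**5. Sex: what would that do to the results?** Two quantities must be kept apart.

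- *Per-visit group difference.* The shift is roughly imbalance × sex effect. For assumed gaps of 5 to 30 points and effects of 0.2 to 0.5 SD, it runs from 0.05 × 0.2 = 0.01 SD to 0.30 × 0.5 = 0.15 SD.
- *Change from baseline, which defines every endpoint in the supplement.* Sex does not vary over time. Entered as a main effect beside a random intercept, it cancels from within-participant differences, so with complete data the group-by-time contrast is unchanged. A simulation confirmed this, with assumed values of 27 and 30 participants, three visits, an expected 20-point sex gap and a 0.5 SD sex effect. With complete data the contrast moved by less than 1e-14. With four Enhanced Mel participants missing after baseline it moved by about 0.005 SD on average and at most 0.03 SD. The per-visit difference moved by about 0.10 SD, as 0.20 × 0.5 predicts.

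**The case against.** The strongest reply is that little has been lost. The pupil data were collected at every laboratory visit and, by the legend, are plotted with confidence intervals. The supplement says that its model was applied to every outcome variable, which could be read to include the PIPR. The figure image and the main report are not among the documents, so a between-arm result may exist elsewhere. This stands as a limit on the point: what is missing is the secondary-outcome status and any described between-arm analysis, not the data. It does not answer the point, because the PIPR is listed as no outcome, sits under a separate heading with a different method, and has no model estimate in these documents.

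Several stronger readings are tempting and are not supported:

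- *The legend presents the rise as an effect of the light.* It does not. It describes an increase in one arm and makes no causal or between-arm statement. A reader may still infer one, which is why the wording matters.
- *Different people were measured at each visit.* The counts show one cohort with a few missing values.
- *The covariates were chosen after the data were seen.* The supplement says that the analysis plan was settled before the analyses began. What is absent is a reason for differing from the protocol.
- *The primary results are unreliable because sex is missing.* No primary results are in these documents, omitting a baseline covariate does not itself bias a randomised comparison, and the change contrasts barely move. The model otherwise matches 6.2 in type, fixed effects and four of the five named covariates.

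**Conclusion.** The point holds in two parts of unequal weight.

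The main part should be fixed. A protocol secondary outcome that serves the trial's secondary aim has no described between-arm analysis at weeks 4 and 6, while a legend states a favourable direction in one arm. The documents support no conclusion either way about whether the enhanced light raised melanopsin function relative to the daylight condition. With 25 to 27 per arm, the 95% interval for that difference would extend about 0.55 SD to each side. This rests on the supplement being a complete description of the PIPR analysis; a result in the main report would reduce the point to a cross-reference.

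The sex mismatch is minor. It is real and unexplained, but under the assumed values its effect on change from baseline is of the order of 0.005 SD. It falls mainly on per-visit group differences, such as those tabulated in Table S1, by up to about 0.15 SD in the assumed range.

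**What to change.** - List the 6s PIPR at weeks 4 and 6 as a secondary outcome in the supplement's Endpoints section, or state that its status changed, when and why.
- Fit the protocol 6.2 mixed model to it (group, time, their interaction and the named covariates, with baseline as a level of time). Report the between-arm difference in change at weeks 4 and 6 with 95% CIs, and the number contributing at each visit.
- Unless that contrast supports the statement of an increase in the Figure S2 legend, remove it or label it descriptive and within-arm.
- Report the mixed models with sex included as 6.2 specifies. Alternatively, disclose and justify its omission and give the sex-adjusted results as a sensitivity analysis.
- Any analysis of baseline PIPR as a modifier of the light effect is an optional addition beyond the protocol and should be labelled exploratory.

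The cost is one covariate (one degree of freedom per model) and one further model on data already collected. The exploratory modifier, if wanted, would need further terms.
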